### Secondary endpoints

Secondary objectives arepercentage of patients with a pain reduction of at least 3 points on VAS at week 2 and 6 weeks after start of treatmentlocal tumor control, measured by longitudinal CT/MRI scans done at FUs by assigning one of the following lesion states: stable, osteoradionecrosis, pathological fracture, sintering progression, local relapsefrequency of re-intervention or salvage therapies to the treated sitesecondary fractures/sintering progressionoverall progression-free survivaladverse eventsincidence of cement leakage (including direction of leakage; symptomatic vs. asymptomatic)skin toxicity/wound healing, documented by regular imaging of the scarquality of life, assessed by completion of EORTC QLQ C30 and BM22 questionnaires

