#### Local tumor control, progression-free survival

At each follow-up visit (after 6 weeks, 3 months and thereafter each 6 months), there will be either a MRI or CT scan of the (complete) spine to determine the response of the treated lesion (stable, osteoradionecrosis, pathological fracture, sintering progression, local relapse) and to monitor for new metastases to other regions of the spine (we recommend the same diagnostic routine, which led to the treatment). Local control is defined as time span between randomization and local progression. Local progression is assessed either by serial CT or MRI scanning. Indicators for local progression in CT scans are:increase in size of osteolytic areasdevelopment of epidural diseaseprogressive sintering/fracture of the treated vertebral body

Once progression is suspected in CT scans, a contrast-enhanced MRI should be performed, whereas indicators of progression areincrease in the T2-signalepidural disease

It has to be considered that MRI and PET may show false-positive signals when the time to surgery is less than 6 months, whereas an epidural disease is the clearest indicator. When in doubt the PI and the steering committee have to decide on the case.

Overall progression-free survival is defined as time from randomization to any (confirmed) tumor progression or death by any cause.

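### Collapse of the treated vertebra seen on CT alone can be called local progression, which could favour the cemented arm on local control even with equal tumour control

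*Protocol article*

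**What the plan says.** All references are to the protocol article. Under *Local tumor control, progression-free survival*, the endpoint is defined thus: "Local control is defined as time span between randomization and local progression". On method it says: "Local progression is assessed either by serial CT or MRI scanning". Three CT indicators follow, without ranking: growth of osteolytic areas, new epidural disease, and progressive "sintering/fracture of the treated vertebral body". The next step reads: "Once progression is suspected in CT scans, a contrast-enhanced MRI should be performed". The MRI indicators are a rise in T2 signal and epidural disease; sintering is not among them. The section cautions that "MRI and PET may show false-positive signals when the time to surgery is less than 6 months", and closes with: "When in doubt the PI and the steering committee have to decide on the case". Overall progression-free survival, in the same section, is tied to tumour progression qualified by the word *confirmed*, or to death.

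The same section opens with a different classification, in which each treated lesion is graded as "stable, osteoradionecrosis, pathological fracture, sintering progression, local relapse". *Secondary endpoints* repeats it: local control is measured by "assigning one of the following lesion states: stable, osteoradionecrosis, pathological fracture, sintering progression", with local relapse as a further state. That list also carries secondary fractures and sintering progression as a separate endpoint.

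*Arm a: Kypho-IORT* specifies cement augmentation by kyphoplasty or vertebroplasty. *Arm B* is external beam radiotherapy alone. The *Discussion* names structural stability and local tumour control as two distinct results of Kypho-IORT in the phase I/II trial.

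**The concern.** Vertebral collapse is kept apart from relapse in one place and is an indicator of local progression in another, and no rule says which governs the endpoint. This matters because the arms differ in mechanical support. Cement is placed in Arm A only, and vertebrae with sintering of up to 50% may enter either arm under the *Exclusion criteria*. If collapse without tumour growth can end local control, part of the arm comparison measures the cement and not the effect of treatment on the tumour.

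The trial was set up, according to the *Background*, to see whether the technique might replace standard care, and the good local progression-free survival in the phase I/II trial is given as the reason. A local-control difference will be read as an oncological result, so it should reflect tumour.

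**Working it through.** **Reading the text.** Take a patient whose treated vertebra collapses further, with no growth of osteolysis and no epidural disease.

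- *Followed by CT, CT taken as sufficient:* an event. Support: the indicator is listed alongside the two tumour signs, either modality is accepted, the MRI is recommended and not required, and confirmation is absent from the local-control definition.
- *Followed by CT, MRI taken as decisive:* no event, unless the MRI shows a T2 rise or epidural disease.
- *Followed by MRI from the start:* no event, because collapse is not an MRI indicator. The article recommends that each patient keep the imaging routine that led to treatment, so the same collapse can be classified differently by modality.
- *Lesion-state list:* sintering progression or pathological fracture, not local relapse.

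**Planned figure.** The article states no expected rate or power for local control in this trial. Its sample-size figures (22 per arm, power 0.817) concern day-1 pain and do not depend on this definition, so there is nothing to reproduce here.

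**Illustration if CT suffices.** Let t be the proportion with tumour progression, equal in both arms, and s the proportion with a collapse-only event. Assume independence, no MRI filter, and no deaths or dropout. No sintering rate is given for either arm, so every s is an assumption, as is t = 10%.

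Apparent failure = 1 − (1 − t)(1 − s). Spurious gap = (1 − t)(s_B − s_A).

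| t | s_A | s_B | Failure A | Failure B | Gap (points) |
|---|---|---|---|---|---|
| 10% | 2% | 10% | 1 − 0.90 × 0.98 = 11.8% | 1 − 0.90 × 0.90 = 19.0% | 7.2 |
| 10% | 5% | 15% | 1 − 0.90 × 0.95 = 14.5% | 1 − 0.90 × 0.85 = 23.5% | 9.0 |
| 10% | 2% | 20% | 11.8% | 1 − 0.90 × 0.80 = 28.0% | 16.2 |

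With 54/2 = 27 patients per arm, these gaps amount to 0.072 × 27 = 1.9 up to 0.162 × 27 = 4.4 patients.

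**Sensitivity to t.** The *Background* offers two anchors: 100 − 93.8 = 6.2% (12-month local progression-free survival in the phase I/II trial) and 100 − 77 = 23% (mean local control in the radiotherapy series). Each is applied to both arms with s_A = 2%. Local control is (1 − t)(1 − s), and the hazard ratio is ln(LC_A)/ln(LC_B), assuming proportional hazards.

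| t | LC in A | s_B = 5% | s_B = 10% | s_B = 20% | s_B = 30% |
|---|---|---|---|---|---|
| 6.2% | 91.9% | 89.1%, HR 0.73 | 84.4%, HR 0.50 | 75.0%, HR 0.29 | 65.7%, HR 0.20 |
| 23% | 75.5% | 73.1%, HR 0.90 | 69.3%, HR 0.77 | 61.6%, HR 0.58 | 53.9%, HR 0.46 |

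**If sintering alone cannot establish progression,** collapse-only events drop out of both arms, the gap is 0 and the hazard ratio is 1.00 in every row.

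**The case against.** The best defence is that the section, read as a whole, treats a CT finding as suspicion. The MRI that should follow uses criteria that omit sintering, doubtful cases go to the investigator and steering committee, and the lesion states are recorded separately, so an analysis without collapse-only events stays possible. Collapse of an osteolytic vertebra can also be a sign of regrowth, so listing it as a prompt for work-up is reasonable.

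Much of this stands, and it rules out four stronger readings that a reader might infer:

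- *That sintering is counted as progression and cement therefore improves local control.* The text permits the call but does not plainly make it. The direction is plausible from the mechanism, but the documents give no rates by arm.
- *That overall progression-free survival inherits the bias.* That endpoint asks for confirmed tumour progression, so it is affected only if a sintering-based call is accepted as confirmed.
- *That post-surgical false-positive MRI signals add to the advantage of Arm A.* Surgery is in Arm A, so false positives would add apparent failures there. They are a separate distortion in the opposite direction, and the net effect is unknown.
- *That the illustrated gap explains the 93.8% against 77% in the Background.* Those figures come from different sources, the second without a stated time point, and the article does not plan on their difference.

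Nor is overlap between two secondary endpoints an error in itself. What the defence does not answer is that the MRI is not required, confirmation is missing from the local-control definition, and adjudication applies only in doubt, with no criterion for isolated collapse.

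**Conclusion.** The point holds in a limited form. The article allows progressive collapse seen on CT alone to be called local progression, and this conflicts with its own separation of collapse from relapse. Because cement is confined to Arm A, the component can favour that arm at equal tumour control. The size cannot be determined from the documents. It is 7 to 16 points under the assumed 10% tumour progression and sintering of 2–5% against 10–20%, and zero if sintering alone cannot establish progression. Severity is moderate. Local control is one of several unranked secondary endpoints, and a must-fix rating would be too strong.

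**What to change.** Reconcile *Secondary endpoints* with *Local tumor control, progression-free survival* for endpoint classification; imaging schedules and patient care need not change.

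1. In both arms and for both modalities, require tumour evidence for local progression: osteolytic growth, epidural disease, or confirmation on the MRI the plan already calls for.
2. Do not let a T2 rise alone suffice within 6 months of surgery. Since only Arm A has surgery, apply the same window from the start of treatment in Arm B, so that the rule does not create a new arm difference.
3. Report sintering or fracture without such evidence only under the secondary fractures/sintering endpoint.
4. Keep the current composite as a sensitivity analysis.

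The cost is wording and re-labelling of states already recorded. There will be fewer local-progression events, and some tumour-driven collapse may be missed; the sensitivity analysis covers that.

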#### Assessment of adverse events

At day 1, week 2, week 6, month 3 and each 6 m follow-up visit, a physical examination of the surgical scar /irradiation field will be performed to grade any of the following toxicities: dermatitis radiation, wound infection, scar, pigmentation, telangiectasia or other skin toxicity. In case of any skin toxicities, a photo will be acquired. A neurological examination will be performed to detect paresthesia, sensory numbness, motor weakness and paresis. An adverse event (AE) is then defined as any unfavorable and unintended sign (including an abnormal laboratory finding), symptom, or disease temporally associated with the use of a medical treatment or procedure regardless of whether it is considered related to the medical treatment or procedure (attribution of unrelated, unlikely, possible, probable, or definite will be interrogated for at each contact between the responsible investigator and the study subject until the end of the study). Ongoing AEs will be followed until recovery. Wherever possible, adverse events will be reported on the basis of CTC-AE v4.0.

A pre-existing disease or symptom (including pathological laboratory values) will not be considered an adverse event unless there will be an untoward change in its intensity, frequency or quality. This change will be documented by an investigator.

#### Serious adverse events (SAE)

Serious adverse events (SAEs) are defined as any event that is fatal, life threatening, causes or prolongs hospitalization; causes disability or incapacity or requires medical intervention to prevent permanent impairment or damage, or any grade 4 toxicity. Only SAEs that are judged to be related to surgery or irradiation by the local study center are reported.

In case of death an autopsy should be done to clarify the cause of death.

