### Arm a: Kypho-IORT

Kypho-IORT will be carried out under general anaesthesia as extensively described before [8–11]. All patients will be placed in prone position on a radiolucent table. An intraoperative low-energy x-ray device (Intrabeam®, Carl Zeiss Meditec AG, Oberkochen, Germany) will be used for intraoperative radiotherapy, the centre of the metastasis shall be chosen for the isocenter of the radiation.

The cement augmentation can be performed either as kyphoplasty or in a vertebroplasty technique. Each patient must receive early post-operative imaging of the treated vertebra to assess any leakage of cement. The direction of leakage and the clinical symptoms associated (symptomatic vs. asymptomatic) must be documented at this stage.

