### Arm B: external beam radiotherapy

Patients randomized into arm B will receive conventional external beam radiotherapy, either as fractionated radiotherapy with 30 Gy delivered in 10 fractions of 3 Gy or as single-dose irradiation with 8 Gy. Each center must select and adhere to one treatment option (fractionated or singe-dose irradiation). Radiotherapy can be given as per established local standards (3D-conformal radiotherapy or intensity-modulated radiotherapy, local standards for target volume and risk organ delineation, local dose constraints). Patients will need to be seen at least once weekly by physicians and evaluated for adverse reactions.

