#### Investigator withdrawal

The steering committee is allowed to close the study ahead of schedule.

Other termination criteria include:insufficient patient recruitmentunexpectedly severe toxicities (second Grade IV toxicity within the study)unexpected findings which prevent the continuation of the study for ethical and/or medical reasons (new benefit/risk analysis)

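### SAEs, including grade 4 toxicities, are reported only if the local centre judges them related, so the study-wide criterion of a second Grade IV toxicity can be missed or delayed

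*Protocol article*

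**What the plan says.** Four sections of the protocol article bear on the point.

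- **Assessment of adverse events.** An adverse event is defined "regardless of whether it is considered related to the medical treatment or procedure". Causality is still recorded, on five levels: "attribution of unrelated, unlikely, possible, probable, or definite will be interrogated for at each contact".
- **Serious adverse events (SAE).** Seriousness is defined without reference to causality and extends to "or any grade 4 toxicity". A filter follows: "Only SAEs that are judged to be related to surgery or irradiation by the local study center are reported".
- **Individual withdrawal.** Grade IV skin, bone and nervous system toxicity, the last exemplified by paresis, are grounds for ending a patient's treatment. No relatedness condition is attached. The reason goes into the patient's file.
- **Investigator withdrawal.** The steering committee may close the study early. One listed termination criterion is the "second Grade IV toxicity within the study". The text does not say whether the toxicity must be judged related, who counts, or from which data.

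The arms are easy to tell apart. In arm A, "Kypho-IORT will be carried out under general anaesthesia"; in arm B, "Patients randomized into arm B will receive conventional external beam radiotherapy". The article describes no blinding and no central or blinded review of relatedness. Adverse events are a secondary endpoint.

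**The concern.** The termination criterion is a count across all centres of a multicentre trial, so events have to travel from the sites to one body. The only SAE reporting rule in the article lets a single site's opinion end that journey. With a threshold of two, one event not passed on is enough for the criterion not to be met when it should be.

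Attribution is hard in this population. The section on local tumour control lists progressive sintering or fracture and epidural disease as signs of progression, while paresis is an example of Grade IV toxicity in the withdrawal section. The same clinical picture can be called disease or treatment. The SAE section itself asks for an autopsy to settle the cause of death, which concedes that the cause may be unclear. Doubtful progression calls are referred to the principal investigator and the steering committee, but no such referral is given for SAE relatedness.

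Two things are at stake: the working of a safety criterion, and the meaning of any summary of reported SAEs by arm, since each entry depends on a judgement made with knowledge of the arm.

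**Working it through.** **Side by side**

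1. All adverse events are within scope, whatever the cause, and attribution has five levels.
2. Every grade 4 toxicity is an SAE.
3. An SAE is reported only if the local centre calls it related. This is a yes/no decision, and no cut-point on the five levels is given, so whether an event rated possible or unlikely is reported is left to each site.
4. The termination criterion counts Grade IV toxicities in the whole study, with no relatedness condition and no named data source.

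From 2 and 3, a Grade IV event judged unrelated is not reported as an SAE. From 4, it may nevertheless belong in the count. No section links the adverse event records or the patient files to that count.

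**Inputs for the illustration**

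The article gives no Grade IV rate and no share of events judged related, so there is no stated figure to reproduce on this point. The planned total of 54 patients comes from the sample size section. Everything else is assumed:

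- s, the probability that a Grade IV event is judged related: 0.9, 0.8 or 0.6, independently between events;
- p, the Grade IV rate per patient: 2%, 5% or 10%;
- q, the share of Grade IV events judged related and hence reported: 0.9, 0.75 or 0.5.

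**Exactly two Grade IV events**

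P(at least one filtered out) = 1 − s².

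- s = 0.9: 1 − 0.81 = 0.19
- s = 0.8: 1 − 0.64 = 0.36
- s = 0.6: 1 − 0.36 = 0.64

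**Chance that the count reaches two among 54 patients**

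Take at most one event per patient and let r be the rate that enters the count: r = p if all events are counted, r = p × q if only reported ones are. Then P(at least 2) = 1 − (1 − r)^54 − 54 r (1 − r)^53.

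| Assumed Grade IV rate | All counted | q = 0.9 | q = 0.75 | q = 0.5 |
|---|---|---|---|---|
| 2% | 0.294 | 0.254 | 0.194 | 0.102 |
| 5% | 0.759 | 0.705 | 0.606 | 0.392 |
| 10% | 0.976 | 0.961 | 0.920 | 0.759 |

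**Summary by arm**

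Suppose the true rate is 10% in both arms, and 90% of events are judged related in arm A and 50% in arm B. The reported rates are 0.10 × 0.9 = 9% and 0.10 × 0.5 = 5%. Swapping the two shares reverses the difference. The document supports neither direction.

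Sample size and power do not enter this point.

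**The case against.** Several objections have force.

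- **The arms are filtered differently.** A reader might infer this, but the document does not say it. One written rule covers both arms and names both surgery and irradiation, and both arms have the same scheduled scar or field examinations and neurological examinations. Differential attribution is a risk of open-label judgement, not a documented fact.
- **Unreported events never reach the committee.** This too is more than the text supports. Events judged unrelated remain within adverse event recording, and a Grade IV event that ends treatment is noted in the patient's file. What can be said is that no route from those records to the count is stated.
- **The SAE and termination sections flatly contradict each other.** That depends on reading toxicity as any event. If it means harm from treatment, both sections concern related events and the conflict largely disappears. The count then still rests on one site's unreviewed attribution.
- **The endpoints do not depend on SAE reports.** No between-arm SAE test is specified. The secondary endpoint is adverse events, which carries no causality filter. Deaths enter the survival endpoints and fractures have their own endpoint, neither of which requires relatedness. This stands, and it limits the by-arm concern to summaries of reported SAEs.
- **The percentages are not trial evidence.** They are assumed and conditional, and they take the adverse event records to contribute nothing to the count. A criterion missed at the second event may only be delayed until a later one, and the committee has other grounds for closing the study.
- **There is a plausible reason for the filter.** In metastatic cancer, many deaths and admissions will be due to disease. Reporting may also mean onward or expedited reporting, with the detail left to the full protocol.

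The last objection may explain the filter, but it does not repair its link to the Grade IV count. The article states the filter as a rule; it is not merely silent.

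**Conclusion.** The concern holds in limited form. Under the stated rule, a Grade IV event that a site attributes to the cancer has no stated reporting route to the steering committee, so a two-event, study-wide criterion can be missed or delayed. This remains true if toxicity is read as treatment-related, because relatedness is then decided locally, with knowledge of the arm and without review. Knowledge of the arm is inferred from the interventions; the article does not state it.

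The size cannot be taken from the document. On assumed values, the chance of losing at least one of exactly two events runs from 0.19 to 0.64. At an assumed 5% Grade IV rate, the chance of the count reaching two falls from 0.76 to between 0.39 and 0.71. These figures rest on independent judgements and on a count fed only by reported SAEs. For summaries of reported SAEs by arm there is a risk of distortion, of unknown direction and size. The primary endpoint is untouched. The text should be changed, but the defect does not undermine the trial.

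**What to change.** - Replace the filtering sentence in the SAE section: all SAEs, including every Grade IV event, in both arms from randomisation, are reported to the steering committee whatever the local attribution. Record the five-level attribution with each report as a variable.
- Summarise SAEs by arm for all events, with related events as a subset, and state which attribution levels count as related.
- Reconcile the sections on adverse events, SAEs, individual withdrawal and investigator withdrawal: which Grade IV events count towards termination, who counts them, and from which data. The threshold and the stopping rule themselves are for the sponsor and steering committee; nothing is proposed here.

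The cost is more SAE forms, many of them for disease progression, in a trial of 54 patients with follow-up of up to 5 years. The events and their attribution already fall within adverse event recording, so the added work is mainly in passing them on. Sample size and power do not change.

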#### Quality of life

QoL will be determined using the EORTC quality of life C30 and the bone metastasis module questionnaire (EORTC-QLQ-C30/BM22). The questionnaires should be completed before.

treatment and during follow-up visits. The questionnaires have 30 respectively 22 questions and require approx. 10 min to complete. Even if the patient progresses or recurs before the last scheduled QoL assessment, QoL forms should still be completed.

